## Abstract

**Background:**

Total hip arthroplasty (THA) is one of the most successful orthopaedic procedures. Because of the increasing number of THAs, a growing demand for faster recovery and a greater emphasis on cost-effectiveness, minimally invasive THAs have been introduced in the last decades. The direct anterior approach is a minimally invasive, tissue-sparing approach in which intermuscular planes are used. Theoretically, this approach should result in a faster recovery of physical functioning and higher health-related quality of life.

**Methods/design:**

A randomised controlled trial will be performed. Patients will be randomly allocated to undergo THA by means of the anterior or posterolateral approach. Both the intervention and control group will consist of two subgroups: 1) patients with a good bone stock who will receive an uncemented femoral stem, and 2) patients with a poor bone stock who will receive a cemented femoral stem. Patients between 18 and 90 years with primary or secondary osteoarthritis will be included. Physical functioning and health-related quality of life will be assessed by means of questionnaires. Additionally, performance based tests will be performed to objectively assess the physical functioning. Cost-effectiveness will be assessed by obtaining data on medical costs in and outside the hospital and other nonmedical costs. Measurements will take place preoperatively, two and six weeks, three months and one year postoperatively.

**Discussion:**

There is some evidence that the anterior approach results in reduced tissue damage and faster recovery in the direct postoperative period, compared to the posterolateral approach. However, there is still a lack of well-designed studies that have confirmed the better outcomes and cost-effectiveness of the anterior approach. Therefore, the purpose of this study is to assess the physical functioning, health related quality of life and the cost-effectiveness of the anterior approach, compared to the conventional posterolateral approach.

**Trial registration:**

Netherlands Trial Registry, number 5343 (registration date April 12, 2015)

**Electronic supplementary material:**

The online version of this article (doi:10.1186/s12891-016-1322-2) contains supplementary material, which is available to authorized users.

## Background

Total hip arthroplasty (THA) is considered to be one of the most successful orthopaedic interventions of the past 40 years, with 10-year survival rates exceeding 90% [1, 2]. The number of THAs has increased rapidly during the last decade, because of ageing of Western societies and an increase of the incidence of obesity. Additionally, THA is nowadays not only performed in elderly patients, but also in younger patients who are still members of the working population. Driven by this growing demand for THA, together with a greater emphasis on cost-effectiveness in health care and patients’ higher expectations of shorter hospital stays and faster recovery, alternative surgical procedures have been developed to improve the success of THA. Minimally invasive total hip arthroplasty (MIS THA) is one of these developments.

MIS THA aims at minimising damage to soft tissues during surgery in order to enhance postoperative recovery and, consequently, accelerate the return to normal daily functioning [3]. Despite the increase in use of MIS THA, its risks and benefits are still an ongoing debate in the orthopaedic community. There is a wide variety of MIS THA procedures, which have shown variable results [4]. However, these variable results for MIS THA can for a large part be contributed to the fact that some of these so-called minimally invasive techniques, are actually not minimally invasive. There are patent differences between using an alternate surgical approach intended to gain access to the hip joint through less soft-tissue dissection and using intermuscular planes (i.e. a tissue-sparing approach). Hence, when one looks critically at the literature on MIS THA, it appears that the term “minimally invasive” is often used for a conventional THA technique performed through a smaller skin incision, with at least the same amount of tissue damage under the skin compared to the conventional approach (i.e. mini-incision THA) [5].

The anterior approach for THA is a minimally invasive, tissue-sparing technique. Conceptually, the anterior approach should cause less tissue damage compared to the conventional posterolateral approach, as intermuscular planes are used without muscle dissection [6]. Moreover, by (partially) dissecting several muscles around the hip, the posterolateral approach is more prone for instability postoperatively. Whereas with the anterior approach, the musculature for pelvic stabilisation remains undisturbed [7]. These muscles also play an important role in gait function. Hence, theoretically, the anterior approach should result in a faster recovery of physical functioning and, thus, a higher health-related quality of life.

Little research has been conducted so far on the implications of MIS THA, and especially the direct anterior approach (DAA) for THA, in elderly patients [8]. The skeletal musculature of elderly patients possesses a higher vulnerability and a reduced regenerative capacity [9]. Additionally, elderly patients are characterized by a higher incidence of postoperative fatty muscle atrophy, which is associated with reduced muscular function [9]. More importantly, patients who underwent THA through a conventional approach had a significantly higher grade of muscle atrophy compared to older patients following MIS THA. Muller et al. [9] concluded that especially older patients seem to benefit from a minimally invasive approach. Whether the previously mentioned results are also applicable for the anterior approach, is still unknown.

The ability to ambulate independently is an important hospital discharge criterion since a proper gait function is crucial to perform several activities of daily living independently. Thus far, there are no studies that compare the cost-effectiveness of the direct anterior approach. Despite this, there is some evidence that accelerated postoperative care can be cost saving [10]. In this respect the anterior approach, because of its muscle sparing character and potentially faster recovery, might not only be a clinically effective but also a cost-effective surgical technique for THA.

There is however a lack of well-designed studies, and thus of objective evidence, on the effectiveness of the anterior approach. The scarce, but promising evidence that is available is derived from retrospective case series or small prospective trials [11–14]. Little is also known about whether older patients even benefit more from the anterior approach. Moreover, little information is present about the cost-effectiveness of the anterior approach for THA. Hence, the aim of this study is to conduct a randomised controlled trial to determine the clinical and cost-effectiveness of the direct anterior approach compared with the conventional posterolateral approach for THA.

## Methods/Design

### Study design

A prospective randomised controlled trial will be executed. Patients will be randomly allocated to undergo THA by means of the direct anterior approach or the posterolateral approach.

### Study population and recruitment procedure

Patients will visit the outpatient clinic at the Department of Orthopaedic Surgery at the Martini Hospital Groningen where they will receive oral and written information about the study. After screening according to the in- and exclusion criteria (Table 1). Patients with a previous surgery of the ipsilateral hip, complaints or a hip prosthesis of the contralateral hip and symptomatic osteoarthritis of the knee will be excluded, because these factors may influence the gait analysis measurements and the questionnaires when there are complaints or limitations in functioning because of these factors. Pfirrmann et al. showed that patients with symptomatic complaints after THA have more muscle atrophy [15]. Furthermore, evidence exists that atrophic muscle might not regenerate postoperatively and these factors are important in the assessment of physical functioning [16]. Moreover, because patients of 90 years and above have other comorbidities and are usually not operated in our hospital, we will exclude these patients.

**Table 1 Tab1:** In- and exclusion criteria

Inclusion criteria	Exclusion criteria
- Age between 18–90 years; - Indication for THA is primary or secondary symptomatic osteoarthritis	- A history of previous surgery on the ipsilateral hip; - complaints of the contralateral hip; - a hip prosthesis at the contralateral side; - symptomatic osteoarthritis of the knee; - peripheral neuropathy; - (active) arthritis (e.g. rheumatic disease); - a history of CVA; - COPD GOLD III or IV - NYHA class III or IV - cognitive impairments. - not able to fill in questionnaires in the Dutch language

*Abbreviations: THA* Total Hip Arthroplasty, *CVA* Cerebrovascular Accident, *COPD* Chronic Obstructive Pulmonary Disease, *NYHA* New York Heart Association

After the patients have had a consideration period of two weeks, they will be included in the study. They will then be randomised into either the control group (posterolateral approach) or the intervention group (direct anterior approach) by random allocation. Both the intervention and control group will consist of two subgroups: a subgroup with patients with a good bone stock that will receive an uncemented femoral stem and a subgroup of patients, with less good bone stock that will receive a cemented femoral stem. The quality of the bone stock will be determined by routine preoperative pelvic X-rays. Since there are no studies that describe characteristics on which the type of femoral component can be chosen on pelvic X-rays, the quality of the bone stock will be determined by the orthopaedic surgeons. The main determinant will be the thickness of the femoral cortices. Because bone mineral density, and thus bone quality, decreases with age, this will also be a determinant in the choice for the stem component. Generally, patients with an age of 70 years or more will receive a cemented femoral stem. The age of 70 years is chosen because of the lower revision rates and cost-effectiveness with cemented femoral stems in this age group [17]. However, this cut-off point remains arbitrary since the life span of the older population can give misleading results on revision rates. Also, because of the longer life span of the younger population, a revision of the femoral because of aseptic loosening, will be less demanding with an uncemented femoral stem.

Two random allocation sets (for the uncemented femoral component and for the cemented femoral component) of the type of THA approach will be generated by means of a computer by an independent person (research coordinator). These allocations are then sealed in consecutively numbered opaque envelopes. Once the patient has given consent to be included in the trial, the THA approach is then randomly assigned by opening the next sealed envelope, for either the uncemented or the cemented femoral stem. After that, the envelope with the matching study number is opened by an independent research nurse who thus is blinded regarding the randomisation sequence. It is not possible to blind the patient for the allocated surgical technique, since the surgical incision site of the studied approaches is different (i.e. on the anterior or posterolateral side of the hip joint).

It is expected that around 30% of the patients are ineligible or refuse to participate in the study. Hence, approximately an inclusion period of 24 months will be needed to include 260 patients.

### Interventions

The orthopaedic surgeons who are participating in this study (*N* = 3) are experienced in performing both the posterolateral and the direct anterior approach. The learning curve for the anterior approach is said to be between the 20 and 100 cases [18–21]. The three orthopaedic surgeons have reached a number beyond the 100 cases and they will perform, or supervise, all THAs in the present study. The anaesthetic, analgesic and postoperative physical therapy protocols will be standardized. Discharge criteria will also be the same in both study groups (Additional file 1).

The type of femoral component that will be placed will be based on the quality of the bone stock. Patients with good firm bone stock of the proximal femur will receive an uncemented stem (Taperloc™, Biomet Corporation, The Netherlands), that will be hammered into the shaft of the proximal femur. Patients with less firm bone stock of the proximal femur will not receive an uncemented stem, because of the risk of periprosthetic fractures during stem insertion. They will get a cemented stem (Stanmore™, Biomet Corporation, The Netherlands). In all groups, a cemented acetabular component (Stanmore™, Biomet Corporation, The Netherlands) will be placed.

#### Intervention group – direct anterior approach

Advantage of the anterior approach is the possibility of using intermuscular planes, avoiding muscle damage by cutting or detaching muscles. The patient is placed in a supine decubitus position. The skin incision is made over, and in the direction of the lateral part of the femoral head and neck. After division of skin and subcutis, the interval between the tensor fasciae latae muscle and the sartorius muscle is identified and the overlying fascia is opened. In this part of the operation care must be taken to avoid damaging the lateral cutaneous nerve, supplying the sensation of the skin on the lateral part of the thigh. The intermuscular plane between the tensor fasciae latae and sartorius muscle is developed further down to the hip capsule. Subsequently the hip capsule is opened, allowing access to the hip joint. Preparation of the hip for implantation of a hip prosthesis can take place now, by in situ performance of the femoral neck osteotomy, removal of the femoral head and reaming of the acetabulum. Next, bone cement (Palacos®, Heraeus Medical, The Netherlands) is pressurized into the acetabular cavity, followed by insertion of the acetabular cup. After reaming of the femur, the femoral component can be placed with or without bone cement, followed by placement of a head on the femoral component, repositioning of the joint and closure in layers. In case of a cemented femoral component, bone cement is pressurized into the femoral cavity before the femoral component of the hip prosthesis is placed.

#### Control group – posterolateral approach

The patient is placed in a lateral decubitus position. The skin incision is made over the greater trochanter to cranial, with a slight curve to posterior. After transection of the subcutis, the fascia latae and the gluteus maximus muscles are split. Next, the short external rotators, namely the piriformis, the inferior and superior gemellus and the obturator internus muscles, are cut at the level of their insertion at the greater trochanter, so this approach is not muscle-sparing. In this phase of the procedure, caution is advised with the sciatic nerve, the main nerve for the lower leg. After retraction of the short external rotators backwards, the hip capsule becomes visible and can be incised, allowing access to the hip joint. Subsequently, the hip joint is then dislocated and the osteotomy of the femoral neck is performed, followed by the removing of the femoral head. The rest of the operation will essentially take place in the same manner as the anterior approach.

### Measurements

Measurements will be performed by an independent investigator. Standard measurement will take place preoperatively, and six weeks, three months and one year postoperatively. As it is hypothesised that the anterior approach is superior to the posterolateral approach in terms of a faster recovery, mainly in the early recovery period (shorter hospital stay, faster return to normal ADL functioning), extra measurements of physical function, gait analysis and economic evaluation will take place two weeks postoperatively. The questionnaire will be sent to the patients a few days prior to the visit or – when patient do not have an email – will be filled in during the clinical outpatient visit. The filling in of the questionnaire will approximately take 30 to 45 min of patients’ time. A CONSORT flow chart is provided in Fig. 1. Demographic data, preoperative diagnosis, height, weight and Body Mass Index (BMI), ASA classification and the Kellgren and Lawrence (KL) score will be recorded preoperatively.

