#### Economic evaluation

An economic evaluation will be conducted to gain insight into cost-effectiveness of the anterior approach compared to the posterolateral approach for THA. After completion of the data collection, the health status, as determined by means of the EQ-5D, will be related to costs in additional economic analyses. These analyses will provide information on the probable cost-effectiveness of the anterior approach compared to the posterolateral approach for THA in the Dutch healthcare system.

The evaluation will be performed from a societal perspective; costs within and outside the healthcare sector will be included. Costs will be registered prospectively, i.e. within the framework of the current study, for all the included patients. A standardised questionnaire on medical costs after THA will be administered at two and six weeks, three months and one year postoperatively. The questionnaire is set up by the Medical Technology Assessment (MTA) and is used in the cost-effectiveness analyses. It contains 11 questions on indirect medical and non-medical issues regarding the THA outside of the hospital. Medical questions include hospital readmissions, visits to the hospital and/or other (paramedical) healthcare workers. Non-medical questions concern patients’ living and working situation.

The direct medical costs, such as the use of the operative theatre, hospital admission and additional interventions (e.g. blood transfusions) will be compared between the two approaches. Most salient cost advantages of the anterior approach are expected in the area of hospitalization costs. Of the various nonmedical costs, informal care costs are assumed to be substantial in the targeted population and will be registered in detail (e.g. visits to the general practitioner, physical therapy). In order to facilitate comparisons with other economic evaluations, unit prices (i.e. the price of one unit of each included cost type) are based on Dutch standard prices [49]. True costs of used resources will be estimated when standard prices are not available.

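### The cost questionnaire is scheduled only after surgery, so the incremental cost cannot be adjusted for preoperative resource use and some precision may be forgone

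*Protocol article*

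**What the plan says.** The Economic evaluation section sets a broad scope: "The evaluation will be performed from a societal perspective; costs within and outside the healthcare sector will be included". It describes the instrument ("It contains 11 questions on indirect medical and non-medical issues regarding the THA outside of the hospital"), adds that "Non-medical questions concern patients’ living and working situation", and says that "informal care costs are assumed to be substantial in the targeted population and will be registered in detail". It times the form explicitly: "A standardised questionnaire on medical costs after THA will be administered at two and six weeks, three months and one year postoperatively". No preoperative administration is listed, and informal care is given no timing of its own.

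The Measurements section describes a standard schedule that includes a preoperative occasion, and adds that "extra measurements of physical function, gait analysis and economic evaluation will take place two weeks postoperatively". Its list of preoperative data runs "Demographic data, preoperative diagnosis, height, weight and Body Mass Index (BMI), ASA classification" and ends with the Kellgren and Lawrence score. It does not say what the demographic data include.

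The EQ-5D, by contrast, has an explicit preoperative measurement in the section on physical functioning and health-related quality of life.

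The Statistical analysis section divides the difference in mean costs by the difference in mean effects or QALYs and describes the uncertainty with 5000 bootstrap iterations. It states no covariate adjustment of costs.

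**The concern.** Patients with symptomatic hip osteoarthritis may already receive informal care or physical therapy, or be off work, before the operation. The Background notes that some THA patients still belong to the working population. In a societal evaluation, any such use that continues after surgery enters the follow-up costs of whichever arm the patient was allocated to. With a raw difference in means, chance differences between the arms in prior use pass into the incremental cost.

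A preoperative value of the same cost items is the natural covariate for removing part of that noise. The effect side of the ratio has its baseline through the EQ-5D, but the cost side has none in the stated schedule. An analysis plan can add a covariate later, but it cannot supply one that was not collected. Cost-effectiveness is part of the trial's stated aim, so its precision deserves some attention.

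**Working it through.** **1. Is the cost form postoperative only?** The article sets timing instrument by instrument. The EQ-5D is placed before surgery and at three later points. The WHODAS II participation subscale is placed at three postoperative points. The cost form is placed at four postoperative points. Read consistently, the cost form has no preoperative administration. Two places are looser. The abstract mentions cost data and then gives one general schedule that includes a preoperative occasion. Measurements calls the two-week economic measurement extra to a standard schedule that also has one. Neither says that cost items are asked before surgery.

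**2. What the plan itself quantifies.** The plan gives no standard deviation, correlation or precision target for costs, so there is no cost figure to reproduce. The only size calculation concerns PASS (70% against 90%, 80% power, alpha 5%). It reproduces at 59 to 62 per subgroup against the stated 60, but it does not bear on this point. What carries over is the number of patients:

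- 260 × (1 − 0.10) = 234 completers
- 234 / 2 = 117 per arm, assuming equal arms

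**3. Gain from adjusting for a preoperative cost.** Let r be the correlation between preoperative and later out-of-hospital and non-medical costs. The documents do not give r, and the values below are assumptions. Under randomisation, linear adjustment multiplies the variance of the cost difference by 1 − r² and the confidence-interval width by √(1 − r²). The equivalent sample size is 234 / (1 − r²).

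| r (assumed) | Variance factor | Width factor | Narrowing | Equivalent N |
|---|---|---|---|---|
| 0.2 | 0.96 | 0.980 | 2% | 244 |
| 0.3 | 0.91 | 0.954 | 5% | 257 |
| 0.4 | 0.84 | 0.917 | 8% | 279 |
| 0.5 | 0.75 | 0.866 | 13% | 312 |

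**4. Total cost.** The table applies to the out-of-hospital and non-medical component. Suppose that component makes up a share s of the variance of total cost, is uncorrelated with hospital cost, and is the only part that preoperative cost predicts. The width factor for total cost is then √(1 − s·r²). Because s is below 1, the gain is smaller than in the table, and it approaches zero when hospital costs dominate.

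**5. Size of a chance imbalance.** If 30% of patients already receive informal care (an assumption), the standard deviation of the between-arm difference in that proportion is √(2 × 0.3 × 0.7 / 117) = 0.060, or 6 percentage points.

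**The case against.** The strongest reply is that nothing here is wrong in the sense of invalid. Allocation is random, the raw difference in mean costs is unbiased, and the bootstrap reflects its uncertainty. The planned analysis uses no baseline cost, so it loses nothing that it would have used. That stands. A reader might infer that the cost-effectiveness result is biased because continuing preoperative use is charged to the approach. The documents do not support this, since such use is balanced in expectation.

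A reader might also infer that work and care status are never recorded before surgery. That goes too far. The demographic data are undefined and may include them, the flow chart is not shown, and the general schedule is loosely worded. The supportable statement is that no such item is named and that the cost form is not scheduled before surgery.

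Other covariates remain available: age, ASA class, stem set and preoperative EQ-5D. Separate allocation sets by stem type, with stem choice generally following age, limit imbalance in age and perhaps in age-related care and work. The exclusion criteria remove several likely causes of heavy prior care. These are partial substitutes, because none of them measures prior care use or work absence. Recall at the two-week measurement would also be possible, though less reliable.

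The size is uncertain. The form concerns matters tied to the operation, so r may be low, and at r = 0.2 the gain is negligible. The article expects the clearest cost advantage in hospitalisation, which preoperative care use may not predict. The ratio also carries uncertainty from its denominator, which this change leaves untouched. These points limit the weight of the concern. They do not alter the schedule as written.

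**Conclusion.** The point holds as a minor design weakness. As scheduled, the societal cost difference cannot be adjusted for prior resource use measured with the trial's own cost items, and some precision may be forgone. Under an assumed correlation of 0.2 to 0.5, the forgone narrowing of the confidence interval is about 2% to 13% for out-of-hospital and non-medical costs, and less for total cost where hospital costs dominate. The documents cannot fix the correlation or the share of each cost component, so they do not show a material loss of precision in the ICER. There is no bias and no contradiction between sections. It is worth changing only because the change is cheap and the value is best collected before surgery.

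**What to change.** Add the applicable healthcare-use, informal-care and work questions to the existing preoperative questionnaire, with a stated recall period matched to that of one of the later forms. The form cannot be given unchanged, because it asks about costs after the operation, including readmissions. If these items are already collected before surgery, the Economic evaluation section should say so.

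In the Statistical analysis section, replace the raw difference in mean costs with an estimate from a regression of cost on approach, stem set and preoperative cost, fitted within each of the 5000 bootstrap samples. The stem set is known for every patient because it determines the allocation set, so including it needs no extra data.

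The cost is minor rewording of the form, a few minutes added to a questionnaire that already takes 30 to 45 minutes, and two covariates in the cost model.
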